## Abstract

**Introduction:**

Heavy goods vehicle (HGV) drivers exhibit higher than nationally representative rates of obesity, and obesity-related comorbidities, in comparison to other occupational groups. Their working environments are not conducive to a healthy lifestyle, yet there has been limited attention to health promotion efforts. We have developed a Structured Health Intervention For Truckers (the SHIFT programme), a multicomponent, theory-driven, health-behaviour intervention targeting physical activity, diet and sitting in HGV drivers. This paper describes the protocol of a cluster randomised controlled trial designed to evaluate the effectiveness and cost-effectiveness of the SHIFT programme.

**Methods and analysis:**

HGV drivers will be recruited from a logistics company in the UK. Following baseline measurements, depots (clusters) will be randomised to either the SHIFT intervention or usual-care control arm (12 clusters in each, average cluster size 14 drivers). The 6-month SHIFT intervention includes a group-based interactive 6-hour education session, worksite champion support and equipment provision (including a Fitbit and resistance bands/balls to facilitate a ‘cab workout’). Objectively measured total daily physical activity (steps/day) will be the primary outcome. Secondary outcomes include: objectively measured light-intensity physical activity and moderate-to-vigorous physical activity, sitting time, sleep quality, markers of adiposity, blood pressure and capillary blood markers (glycated haemoglobin, low-density lipoprotein-cholesterol, high-density lipoprotein-cholesterol). Self-report questionnaires will examine fruit and vegetable intake, psychosocial and work outcomes and mental health. Quality of life and resources used (eg, general practitioner visits) will also be assessed. Measures will be collected at baseline, 6 and 12 months and analysed according to a modified intention-to-treat principle. A full process evaluation and cost-effectiveness analysis will be conducted.

**Ethics and dissemination:**

Ethical approval was obtained from the Loughborough University Ethics Approvals Sub-Committee (reference: R17-P063). Study findings will be disseminated through publications in research and professional journals, through conference presentations and to relevant regional and national stakeholders via online media and at dissemination events.

**Trial registration number:**

ISRCTN10483894.

Strengths and limitations of this studyTo our knowledge, this is the first randomised controlled trial to examine the impact of a multicomponent intervention targeting individual and environmental barriers faced by heavy goods vehicle drivers to lead a healthy lifestyle.The trial will involve a full process evaluation and an economic evaluation.The primary outcome, physical activity, will be objectively measured.Sustainability of the intervention will be examined at 6 months follow-up, following completion of the intervention.Due to the nature of the intervention, participants will not be blinded to their treatment arm, and there is a risk that the secondary outcome self-report measures may be susceptible to reporting bias.

## Introduction

Long-distance heavy goods vehicle (HGV) drivers are exposed to a multitude of health-related risk factors associated with their occupation; as a result, lorry driving has been identified as one of the most hazardous working professions.^1 2^ Drivers’ working environment provides limited opportunities for a healthy lifestyle and unhealthy lifestyle behaviours, such as a lack of physical activity, prolonged periods of sedentary behaviour (sitting), poor diet, a high prevalence of smoking, high volumes of alcohol consumption and irregular sleeping patterns are widespread among this occupational group.^2–5^ Furthermore, long and variable working hours, including shift work, and tight delivery schedules within the logistics and transport industry contribute to psychological stress and sleep deprivation,^6^ which can lead to metabolic disturbances and further promote the uptake of unhealthy behavioural choices.^2 5–8^

Long-distance drivers exhibit higher than nationally representative rates of obesity, with observational data from a sample of HGV drivers from the UK demonstrating that 84% were overweight or obese, compared with 75% of males aged 45–54 years reported to be overweight/obese nationally.^9^ Similar data have been reported from US HGV drivers.^2 10^ The high rates of overweight and obesity in HGV drivers elevates their risk of numerous chronic diseases and conditions, including cardiovascular disease, type 2 diabetes, obstructive sleep apnoea and musculoskeletal disorders.^1 2 10–13^

To compound the high-risk health profile observed in long-distance drivers nationally and internationally,^1 2 10–12^ the driver population in the UK (n=~300 000) has been identified as an ageing workforce (mean age: 48 years).^14^ A recent parliamentary report has highlighted the ‘demographic time bomb’ the UK logistics industry is currently facing and the health impact of an ageing, at-risk, workforce ‘driving a vehicle often referred to as ‘a 40-tonne missile’’.^15^ The UK logistics sector is also experiencing a short-fall in HGV drivers, with barriers to recruitment including the lack of roadside facilities, medical concerns and long hours of work.^16^ Recommendations on how to address this shortfall and attract younger employees to the sector include increasing awareness within the industry of the need to address driver health risks and health behaviours.^15^

A systematic review^17^ of health promotion interventions in truck drivers, including only eight studies, observed that the interventions generally led to improvements in health and health behaviours. However, it was concluded that the strength of the evidence was limited due to poor study designs, with no control groups, small samples and no or limited follow-up periods.^17^ Since the publication of the systematic review, recent studies have examined the impacts of a weight loss intervention in US HGV drivers^18^ and a smartphone application on physical activity and diet in Australian HGV drivers.^19^ While positive findings were observed, the studies were limited by relatively small samples and no comparison groups.

We have developed a Structured Health Intervention For Truckers (the SHIFT programme), a multicomponent, theory-driven, health behaviour intervention designed to promote positive lifestyle changes in relation to physical activity, diet and sitting in HGV drivers. This intervention has been informed by extensive stakeholder engagement, including a qualitative study exploring the perceived barriers to healthy lifestyle behaviours in HGV drivers,^7^ an observational study exploring lifestyle health-related behaviours in HGV drivers and markers of health^3^ and a pre-post pilot intervention^20^ with full process evaluation.^21^ Initial pre-post testing of the intervention revealed the SHIFT programme lead to favourable changes in physical activity and some markers of health.^20^ This protocol paper describes a study which will build on our earlier work and generate new knowledge on the effectiveness and cost-effectiveness of the SHIFT programme, evaluated using a cluster randomised controlled trial (RCT) design with immediate and extended follow-up. Specifically, we will examine the impact of the SHIFT programme on physical activity, sedentary behaviour, fruit and vegetable intake, adiposity, sleep duration and quality, risk factors for cardiometabolic disease, psychosocial outcomes and mental health in a sample of HGV drivers.

### Study aim and objectives

The aim of this study is to evaluate the effectiveness and cost-effectiveness of the SHIFT programme using a cluster RCT.

#### Primary objective

To investigate the impact of the SHIFT programme, compared with usual care, on objectively measured physical activity (expressed as steps/day) at 12 months follow-up.

#### Secondary objectives

To investigate the impact of the SHIFT programme, compared with usual care, at 12 months follow-up on:

time spent in light and moderate-to-vigorous physical activity (MVPA);sitting time;measures of adiposity (body mass index (BMI), per cent body fat, waist-to-hip ratio, neck circumference);blood pressure;cardiometabolic risk markers (eg, glycated haemoglobin (HbA1c), total cholesterol, low-density lipoprotein-cholesterol (LDL-C), high-density lipoprotein-cholesterol (HDL-C));fruit and vegetable intake;sleep;cognitive function and psychophysiological reactivity;psychosocial variables and mental health (eg, anxiety and depression, work engagement, job performance and satisfaction, presenteeism, sickness absence, health-related quality of life and driving-related safety behaviour).

We will also conduct a full process evaluation (secondary objective 10) and a full economic evaluation (secondary objective 11).

## Methods and analysis

### Design

The design of this study is based on guidance from the UK Medical Research Council for developing and evaluating complex interventions,^22^ and this protocol paper has been prepared following the recommendations within the Standard Protocol Items for Randomised Trials statement.^23^ This is a workplace two-armed 12-month cluster RCT, which will incorporate an internal pilot, and include both economic and process evaluations. Clusters (different worksites/depots within the same company) will be randomised, following the completion of baseline measurements, to receive either the ‘SHIFT programme’ or usual care condition. The impact of the intervention will be assessed at 6 and 12 months after randomisation. Figure 1 shows the overall trial design.

**Figure 1 F1:**
[figure not shown]
Trial design and participant flow through the study.

### Setting

This research will take place within the worksite setting of a major international logistics and transport company. The logistics and posts sector is worth approximately £55 billion to the UK economy and currently employs approximately 1.7 million people. Driving is a fundamental occupation within this industry, and drivers and warehouse workers make up the majority of the workforce within the industry.^15^

### Depot recruitment and exclusion criteria

Depots will be included in the study if they contain at least 20 long-distance HGV drivers (see ‘Sample size’ section). Depots containing HGV drivers who make many delivery stops, for example, drivers who deliver consumer goods to domestic customers throughout the day will be excluded. For logistical reasons, depots located within the Midlands region of the UK will be recruited. Our partner company has approximately 40 sites, containing approximately 1700 HGV drivers within this region. These sites are a similar size, and have a similar variation in size, to the company’s national-level data. During recruitment, depots will be informed that they will have a 50% chance of being randomised to a current practice control condition.

### Participant recruitment and exclusion criteria

All HGV drivers within participating depots will be eligible to participate, unless they meet the following exclusion criteria: suffering from clinically diagnosed cardiovascular disease, or mobility limitations that prevent them from increasing their daily activity levels, haemophilia or have any blood-borne viruses. Posters advertising the study will be placed in participating depots for up to 4 weeks prior to the scheduling of baseline measurements. In addition, all drivers within participating depots will receive a letter and participant information sheet informing them of the study. Following the distribution of the study marketing material, researchers will visit participating depots for 1–2 days to enable interested drivers to ask any questions about the study before signing up. On completion of these visits, the researchers will provide a list of drivers’ names who have agreed to participate to their Transport Managers who will then schedule time for participating drivers to attend the baseline (and follow-up) measurements.

Within the UK logistics industry, 1% of HGV drivers are women,^15^ and the proportion of female HGV drivers employed by our partner company reflects this national average. While females will be included in the study, due to the small proportion of the workforce they represent, the included sample of females may not enable statistically meaningful comparisons to examine any influences of sex on the intervention. However, the sample recruited will likely reflect the gender disparities seen in the logistics and transport industry nationally and internationally.

### Sample size

Our earlier exploratory pre-post study revealed that on average HGV drivers achieve 8786 steps/day across both workdays and non-workdays with a SD of 2919 steps.^20^ We have powered this study to look for a difference in step counts (the primary outcome) of 1500 steps/day (equivalent to approximately 15 min of moderately paced walking) between the intervention group and control group. Evidence demonstrates a linear association between step counts and a range of morbidity and mortality outcomes, as well as with markers of health status including inflammation and adiposity, insulin sensitivity and HDL-C in adults.^24–26^ The linear association between step counts and health outcomes indicate that regardless of an individual’s baseline value, even modest increases in daily step counts can yield clinically meaningful health benefits. For example, a difference in daily steps of 1500 steps/day has been associated with around a 5%–10% lower risk of all-cause mortality and cardiovascular morbidity and mortality in the general population and in those with a high risk of type two diabetes, respectively.^27 28^ The proposed level of change has been chosen based on findings from our exploratory pre-post intervention,^20^ while also being clinically meaningful.

Based on a cluster size of 10, a conservative ICC of 0.05 (as there is no previous data to inform this, we have been informed by recommendations of Campbell *et al*^29^), an alpha of 0.05, power of 80% and a coefficient of variation to allow for variation in cluster size of 0.51 (based on partner company data), we will require 110 participants from 11 clusters per arm. From experience in conducting such studies, it is estimated that retention and compliance rates will be approximately 70% at 12 months follow-up; therefore, the sample size will be inflated by 30% to ensure we have adequate power in our final analysis. We will also inflate the number of clusters by two to allow for whole cluster drop out. We will therefore recruit 24 clusters with an average of 14 participants per cluster.

### Intervention—the SHIFT programme

The SHIFT programme is a multicomponent lifestyle-behaviour intervention designed to target behaviour changes in physical activity, diet and sitting in HGV drivers. This 6-month intervention, grounded within the Social Cognitive Theory for behaviour change^30^ consists of a group-based (four to six participants) 6-hour structured education session tailored for HGV drivers, delivered by two trained educators. It includes information about physical activity, diet and sitting and risk factors for type 2 diabetes and cardiovascular disease. The educational component is founded on the approach used in the award winning suite of Diabetes Education and Self-Management for Ongoing and Newly Diagnosed programme (DESMOND) programmes, including the Prediabetes Risk Education and Physical Activity Recommendation and Encouragement programme (PREPARE)^31^ and Let’s Prevent Diabetes programmes,^32^ created by researchers at the Leicester Diabetes Centre and used throughout the National Health Service (NHS),^33^ while being tailored to meet the needs of HGV drivers.^7^ Within the education session participants will not be ‘taught’ in a formal way, but supported to work out knowledge through group discussions and to develop individual goals and plans, based on detailed individual feedback received during their health assessments (see ‘Measurements’ section) to achieve over the 6-month intervention period. The education session is supported by specially developed resources for HGV drivers and participant support materials. The session will include the discussion of feasible strategies for participants to increase their physical activity, improve their diet and reduce their sitting time (when not driving) during working and non-working hours. The content of the educational session is summarised in table 1.

**Table 1 T1:** Outline of the educational component of the SHIFT programme

Section name	Theoretical underpinning	Main aims and educator activities	Duration (min)
Welcome and introduction		Participants introduced to the SHIFT programme and made aware of both content and style of the session.	10
Driver story	Dual process theory,^74^ common sense model^75^	Participants asked about their beliefs about how being a HGV driver can affect health, the causes of these health problems and controllability of these.	30
Risks and health problems	Dual process theory,^74^ common sense model,^75^ social learning theory^76^	Facilitator uses participant stories to support them to work out why they may be at risk of future health problems, and what to do to reduce/manage risk.	55
Physical activity	Dual process theory,^74^ social learning theory^76^	Facilitator supports participants to develop knowledge and skills to support confidence to increase personal activity levels, to set personal goals and self-monitor through the use of Fitbits. Introduction and practical demonstration of the ‘cab-workout’.	80
Depression, sleeping, smoking	Dual process theory,^74^ social learning theory^76^	Facilitator supports participants to develop strategies to manage depression, poor sleep and smoking.	30
Food choices	Dual process theory,^74^ social learning theory^76^	Facilitator supports participants to develop knowledge and skills for food choices to reduce cardiovascular risk factors and improve overall health.	90
Self-management plan	Dual process theory,^74^ social learning theory^76^	Participants supported in developing personal self-management plans.	15
Questions	Common sense model,^75^ social learning theory^76^	Facilitator checks all questions raised by participants throughout the programme have been answered and understood.	5
What happens next	Social learning theory^76^	Follow-up care outlined.	5

HGV, heavy goods vehicle; SHIFT, Structured Health Intervention For Truckers.

During the education session, participants will be provided with a Fitbit Charge 2 activity tracker and encouraged to use this to set goals (agreed at the session) to gradually increase their physical activity predominately through walking-based activity. The Fitbit activity tracker will provide participants with information on their daily step counts and will be used as a tool for self-monitoring and self-regulation. Physical activity tracking using step counters (traditionally pedometers) has been associated with significant reductions in BMI and blood pressure, with interventions incorporating goal setting being the most effective.^34^

The education session will adopt the promotion of the ‘small changes’ philosophy using the Specific, Measurable, Attainable, Relevant, and Timely (SMART) principle^35^ to encourage participants to gradually build-up their daily activity levels, within the confines of their occupation, to meet the current UK Physical Activity guidelines.^36^ For example, participants will be encouraged to establish their own personalised action plan, which may also include making dietary improvements in addition to increases in physical activity, with SMART goals throughout the 6-month intervention. ‘Step count challenges’ (1 week competitions within intervention depots) will run every 6 weeks throughout the 6-month intervention which will be facilitated by local worksite champions. A ‘cab workout’ will be introduced and practised at the education session and participants will be provided with resistance bands and balls, and grip strength dynamometers to take away. Participants will be encouraged to undertake the cab workout during breaks when not permitted to leave their vehicle. Participants will be able to keep the intervention tools beyond the 6-month intervention period, however the company will choose whether to sustain the worksite champion support and step count challenges beyond the 6-month intervention period. A logic model detailing the underlying theory behind the intervention components is shown in figure 2.

**Figure 2 F2:**
[figure not shown]
Logic model for the Structured Health Intervention For Truckers (SHIFT) intervention. BMI, body mass index; CPC, continued professional competence; PA, physical activity.

The structured education session will be delivered by trained personnel from our partner company and by trained members of the research team. These individuals will be trained and mentored by trainers from the Leicester Diabetes Centre. The education sessions will take place within appropriate training rooms within the intervention depots. Personnel delivering the education sessions within each intervention depot will also be trained to act as a local champion, shown to enhance the effectiveness of worksite physical activity interventions.^37^ They will provide ongoing health coach support to intervention participants (during the 6-month intervention period) and be responsible for facilitating the step count challenges.

### Control arm

Depots assigned to the usual practice control arm will be asked to continue with their usual care conditions. Participants in the control depots will receive an educational leaflet at the outset detailing the importance of healthy lifestyle behaviours (ie, undertaking regular physical activity, breaking up periods of prolonged sitting and consuming a healthy diet) for the promotion of health and well-being. Control participants will be requested to complete the same study measurements as those in the intervention worksites, at the same time points. On completion of the study, control depots will be provided with all of the educational material provided to the intervention participants as part of the SHIFT programme. As the intervention will be delivered by trained personnel within our partner company, the company may choose to provide the full intervention (including the education session and health coach support) to control depots on completion of the formal trial.

### Allocation to treatment groups

Clusters (depots within the same company) will be randomised at the worksite level into the two study arms (intervention and control, using an allocation ratio of 1:1). Randomisation into the study arms will take place in two batches; initially the first six clusters (depots) involved in the internal pilot (see below) will be randomised, and in the second batch all of the remaining clusters will be randomised stratified by depot size. Depots will be classified as either small or large based on the median cluster size of all participating depots. In both batches randomisation will take place on completion of baseline measurements and will be done by an independent statistician at the Leicester Clinical Trials Unit.

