### Internal pilot

We intend to conduct an internal pilot study using the first six clusters (depots). The internal pilot will examine issues surrounding worksite and participant recruitment, randomisation, compliance to the primary outcome and retention rates at 6 months following randomisation. After this period, we will continue to the full trial if the following progression criteria are met:

All 24 depots required for the full sample size agree to take part in the study. Six depots will be selected to take part in the internal pilot (three will be randomised to the intervention arm and three to the control arm). This will demonstrate that depot recruitment and intervention delivery is on track.According to our criteria, 84 drivers will need to agree to participate in the internal pilot, based on an average of 14 participants per cluster.An average of 75% of drivers opting into the study, randomised into the intervention arm, attend the education session across the three intervention depots. This figure is based on the intervention uptake rate seen in our exploratory pre-post intervention study (87%),^20^ while also recognising that take-up rates tend to be lower when moving from an efficacy to a larger multicentre effectiveness trial.No more than 20% of participants fail to provide valid data for the primary outcome measure (activPAL-determined step counts) at baseline and at 6 months postrandomisation or withdraw/are lost to follow-up during the 6-month intervention phase. This threshold is necessary as study power requires total withdrawal or loss to follow-up of no higher than 30% during the 6-month intervention and 6-month follow-up (12 months postrandomisation).

If the final two progression criteria are not fully met, strategies to improve these metrics for the full trial will be discussed with the Trial Steering Committee and the study will progress based on recommendations from this committee.

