#### Statistical analysis: main trial

Average daily steps at 12 months will be compared by group using generalised estimating equation models adjusted for baseline values and waking wear time with an exchangeable correlation structure, which adjusts for clustering. For the primary analysis missing data will not be replaced (complete case analysis) but participants will be included in the intervention group in which their depots were randomised irrespective of the intervention actually received (modified intention-to-treat analysis). We have inflated our sample size by 30% to account for potential loss to follow-up and non-compliance with the primary outcome measure. We will compare the baseline characteristics of those who have complete primary outcome data and those who do not. A sensitivity analysis using multiple imputation will be performed to assess the impact of missing outcome data on the results found and to account for uncertainty associated with imputing data (full intention-to-treat analysis). The imputation will be carried out using the command MI in Stata. MI replaces missing values with multiple sets of simulated values to complete the data, performs standard analysis on each completed dataset and adjusts the obtained parameter estimates for missing data uncertainty using Rubin’s rules to combine estimates. The effect size will also be assessed by attendance excluding those who did not attend the full intervention (per-protocol analysis). Secondary outcomes and 6month data will be analysed using similar methodology.

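### The primary model omits depot size and batch, the two factors that restrict the randomisation; the likely cost is a small, conservative loss of precision

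*Protocol article*

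**What the plan says.** The protocol article, under Allocation to treatment groups, restricts the allocation in two ways. First, depots are allocated in two rounds. The pilot depots come first ("initially the first six clusters (depots) involved in the internal pilot (see below) will be randomised"), and the others follow later. Second, "in the second batch all of the remaining clusters will be randomised stratified by depot size". The strata are defined there too: "Depots will be classified as either small or large based on the median cluster size of all participating depots". The overall ratio is 1:1, and the Internal pilot section fixes the first batch at equal numbers: "three will be randomised to the intervention arm and three to the control arm". No size stratification is stated for those six depots.

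Under Statistical analysis: main trial, daily steps at 12 months are compared by GEE, "adjusted for baseline values and waking wear time with an exchangeable correlation structure, which adjusts for clustering". Secondary outcomes and the 6-month data follow a similar method. No other section adds depot size or batch to the model.

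**The concern.** Restricting the allocation makes the arms more alike in size and batch than simple randomisation would. A model without those factors leaves their between-depot variance in the standard error, although the design has largely removed it from the treatment contrast. The reported interval is then wider than it need be, and the test rejects too rarely. With 12 depots per arm, variance at depot level matters.

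Both factors could plausibly affect the outcome. The second batch is expected to follow the pilot's 6-month assessment, so the batches may differ in season, and delivery may change after the pilot. Baseline steps should absorb most of a seasonal effect at 12 months, but less of it at 6 months, when baseline and follow-up fall in different seasons. Whole-depot dropout and the complete-case analysis can also disturb the balance created at randomisation. What is at stake is some power and interval width, not the validity of a positive result.

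**Working it through.** **Inputs from the protocol (Sample size):** target difference 1500 steps/day, SD 2919, ICC 0.05, 10 analysed per cluster, coefficient of variation of cluster size 0.51, alpha 0.05 (two-sided assumed), power 80%, 24 depots recruited. From the allocation and pilot sections: 6 depots in batch 1 (3 per arm) and 18 in batch 2, stratified by size.

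**1. The plan's own figure.**
- Individually randomised: n = 2 × 2919² × (1.960 + 0.842)² / 1500² = 59.4 per arm.
- Design effect: 1 + ((1 + 0.51²) × 10 − 1) × 0.05 = 1.580.
- 59.4 × 1.580 = 93.9 per arm, or 9.4 clusters.
- With t critical values on 2(k − 1) degrees of freedom, 10 clusters per arm give 78.0% power and 11 give 82.2%.

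The stated 110 participants from 11 clusters per arm therefore reproduces. The formula makes no use of stratification, so the required sample size does not change with the fix.

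**2. How large a size or batch effect is plausible.** The between-depot variance implied by the protocol is 0.05 × 2919² = 426,028, an SD of about 653 steps. A binary factor with difference d and split p contributes d² × p(1 − p). Size splits the depots in half (0.25); batch splits them 6 to 18 (0.25 × 0.75 = 0.1875).
- 500 steps/day each: 500² × (0.25 + 0.1875) = 109,375, or 26% of 426,028.
- 1000 each: 437,500, or 103%.
- 1500 each: 984,375, or 231%.
- Size alone explaining 60%: d = √(4 × 0.60 × 426,028) = about 1,010 steps/day, two thirds of the target effect.

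**3. Effect on the analysis.** Simulation, 6,000 runs per scenario, with a weighted cluster-level regression standing in for the GEE. There are 24 depots allocated as described, with assumed analysed sizes of 6 (small) and 14 (large). The size and batch effects are residual to baseline and are added to a between-depot variance at ICC 0.05.

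| Assumed effect of each factor (steps/day) | Type I error, without / with factors | Power, without / with factors |
|---|---|---|
| 0 | 5.1% / 5.2% | 87.7% / 86.5% |
| 500 | 4.4% / 5.0% | 85.0% / 86.1% |
| 1000 | 3.0% / 4.4% | 77.7% / 86.0% |
| 1500 | 2.0% / 5.6% | 66.1% / 86.2% |

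By step 2, the last two rows need more between-depot variance from these two factors than the protocol's ICC allows in total, so they are not realistic headline figures.

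**4. Interval width if size explains 60%.** A separate set of 3,000 simulated trials used a GEE with the Mancl-DeRouen corrected standard error.
- The empirical SD of the estimate (residual-SD units) was 0.1487 without and 0.1452 with the factors.
- The ratio of mean standard error to SD was 1.109 and 1.082.
- Mean standard errors are therefore 1.109 × 0.1487 = 0.1649 and 1.082 × 0.1452 = 0.1571.
- With t values 2.07 and 2.09, the half-widths are 0.3414 and 0.3283, about 4% shorter with adjustment.

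**5. Cluster-level cross-check.** With total between-depot variance held at ICC 0.05 (5,000 runs), the half-widths without and with the factors were:
- 948 and 960 steps with no effect;
- 949 and 928 (2% shorter) with 10% explained by each factor;
- 948 and 859 (9% shorter) with 60% explained by size.

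The gain in the 60% case thus depends on the standard error used as well as on the assumption.

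**The case against.** **The error runs in the safe direction.** This stands. In every scenario the model without the factors rejects at or below the nominal level, apart from simulation noise. A reader might infer from the mismatch that the primary test is invalid; nothing supports that.

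**The standard error is not 11% too large because of the omission.** The ratio of 1.109 in the 60% scenario invites that reading. But the adjusted model's ratio is 1.082, so most of the excess comes from the bias correction itself, which the protocol does not name. The part due to the omission is 1.109 / 1.082 = 1.025, about 2.5%.

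**Baseline adjustment already does much of the work.** This also stands. Each driver's baseline steps are measured before randomisation and are in the model, so stable differences between small and large depots, or between batches, are largely absorbed. Only an effect on the change in steps remains, and that puts the likely loss at the low end of the range.

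**Unstratified pilot depots do not bias the estimate.** A chance size imbalance among six randomised depots is random error. Adjustment would reduce it, but it is not a systematic fault.

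**The analysis plan may settle the covariates.** It may, and it is not shown. But the article does not leave the matter open: it names the covariates and leaves out the factors it uses to restrict allocation. This lowers confidence in the practical impact; it does not remove the mismatch.

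**Conclusion.** The point holds as a mismatch between design and analysis with a modest likely effect. The text is clear: allocation is restricted by batch and by size, and the stated model contains neither.

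The consequence is a possible loss of precision in the conservative direction. Over the range compatible with the protocol's ICC, it runs from a gain of about one power point for the model without the factors (no residual effect) to a loss of about one point (500 steps/day each). The interval gain is about 4% in the GEE simulation if size explained 60% of the between-depot variance, which no section of the protocol supports. A reader might take the larger figures, power falling to 78% or 66%, as the expected loss. They rest on size and batch effects that together exceed all the between-depot variance implied by an ICC of 0.05.

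All sizes rest on assumed effects of size and batch, assumed analysed cluster sizes, and in part a cluster-level approximation to the GEE. Confidence is high on the text and moderate on the impact.

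**What to change.** In Statistical analysis: main trial, add depot size category and batch (pilot or main) as fixed covariates in the primary GEE and in the similar secondary and 6-month models. Use the small/large split from randomisation, and apply it to the six pilot depots as well.

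Make the change together with a small-sample corrected standard error and a t reference distribution suited to about 24 clusters. The two belong together: in the GEE simulation the adjusted model without such a correction rejected a true null in 10–11% of trials, so adding the covariates alone would replace a conservative fault with an anti-conservative one.

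The cost is two cluster-level degrees of freedom (t critical value 2.07 to 2.09) and about one point of power if neither factor is prognostic. No new data are needed, since size and batch are known at randomisation, and the sample size is unchanged. Fixing the covariates in advance also avoids a later choice between adjusted and unadjusted results.
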